### Study outline

TOMO—a collection of current advanced radiotherapy concepts—is a new, image-guided IMRT system that uses CT scanning to emit radiation in a fan-shaped spiral. The application of novel technologies, such as spiral irradiation, image guidance technology, and adaptive radiation therapy, improves the accuracy of radiotherapy and reduces the radiation damage incurred to normal tissues.

#### Equipment and technical support

A three-dimensional treatment planning system (3D-TPS), treatment plan system (TPS), 3D water tank, linear electron accelerators, image fusion software, TOMO, medical linear accelerators, and CT have been provided by the radiotherapy department. Equipment and technical support details are presented in Table 1.

**Table 1 Tab1:** Summary of the new technology project equipment

Device	Device model	Manufacturer	Factory number
3D-TPS	pinnacle3	Philips	20050628
TPS	Pinnacle Smart Enterprise	Philips	20030126
3D water tank	RFA-300	IBA	20021210
Linear electron accelerator	IX6117	Varian	20151217
Image fusion software	MIM	MIM Software	20151125
Linear electron accelerator	UNIQUE	Varian	20140122
TOMO	Tomotherapy HD	Accuracy	20151125
Medical linear accelerators	Clinac IX	Varian	20151203
CT	SOMATOM	Siemens	20140731

*3D-TPS* three-dimensional treatment planning system, *TPS* treatment plan system, *3D water tank* three-dimensional water tank scanning system, *CT* computed tomography, *TOMO* tomotherapy system

#### CT localization scanning method

The patient will lie supine on the special positioning neck and shoulder stand for radiotherapy, and a polymer low temperature-hydrolyzed head, neck, and shoulder thermoplastic body membrane will fix the position. Next, the laser will be positioned on the midline of the head and on both sides (using a special external positioning system). After marking the corresponding reference points on the neck and shoulder thermoplastic body membrane and body surface, the lead particles will be placed for marking. A spiral CT during continuous, calm breathing will scan the whole brain with a pitch of 1 mm, transmitting the data to the TPS via the network prior to performing two-dimensional MRI image acquisition, with layer thickness 1 mm. After the attenuation of the MRI image is corrected with the CT data, the image will be reconstructed using an iterative method.

#### Formulation and implementation of radiotherapy plans

A radiotherapy department chief physician and an experienced image diagnosis physician will outline the radiotherapy target area on the MRI and CT fusion images. The tumor area and gross tumor volume and its extroverted 0.5 cm will be used as the clinical target area clinical tumor volume (CTV). CTV and its extroverted 0.3 cm and tumor motion range will be used as the planning target volume (PTV). Additionally, important functional areas will be outlined, such as the hippocampus, inner ear, and patient lens, and a TOMO radiotherapy plan on the Pinnacle^3^ treatment planning system will be developed. A Varian’s high-energy electron linear accelerator 6-MVX line will be used, alongside tomographic intensity-modulated irradiation field irradiation.

**Fig. 1 Fig1:**
[figure not shown]
Contour of the hippocampal area and specific dose constraints

#### Post TOMO treatment

Patients’ recovery will be monitored (both the experimental group and the control group) as per current medical practice. It may be necessary to perform additional medical treatments following these therapies if side effects appear. Patients undergoing the treatments can be discharged after a few days without any complications.

#### Post TOMO follow-up

After radiotherapy, patients will be reviewed every 2 months for a total of 6 months to evaluate whether they have recurrence and to determine their neurological function status. During 6 months to 2 years after treatment, a re-check will be performed every 6 months. The examination will include a brain MRI test, routine blood tests, and liver and kidney function tests, which will be used to evaluate the effectiveness of the therapy according to the standards set by the committee. The follow-up period for iPFS and OS is 2 years. In addition, we will assess the neurological function and QoL immediately post radiotherapy and at 1 month, 3 months, 6 months, 1 year, and 2 years post RT. The research outline is shown in Fig. 2 and Table 2.

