**Methods:**

This is a randomized, controlled, prospective study including 102 SCLC patients with brain metastases randomized (1:1) to the experimental (whole brain radiation therapy for synchronous brain metastases with irradiation to protect the hippocampus) or control (whole brain radiotherapy for sequential brain metastases to boost irradiation) group. The sample size is calculated through a single-sided test; 102 participants will be required for the main results to have statistical and clinical significance. We aim to provide clinical trial data support for better prognostic treatment options in patients with SCLC and brain metastases. The clinical trial data include both the primary and secondary outcomes; the primary outcome is the intracranial progression-free survival time after the new technology application. The secondary study outcomes include the assessment of neurological function, the quality of life, and the overall survival rate. Follow-up consultations will be conducted every 2 months. After the final patient completes follow-up, the Statistical Product and Service Solutions software will be used for scientific and rigorous data analysis. Version 1.0 of the protocol was implemented on January 1, 2021; the recruitment process for this clinical trial commenced on April 1, 2021, and will end on March 31, 2024.

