### Sample size

It will be necessary to evaluate differences between the two groups; thus, the sample sizes of the experimental and control groups were set as n1 and n2, respectively. The two groups should have the same sample sizes; therefore, a single-sided test was used. The sample size calculation formula was:$${n}_1={n}_2=2{\left[\frac{\left({z}_{\alpha }+{z}_{\beta}\right)\sigma }{\delta}\right]}^2$$

where σ is the overall standard deviation (estimated to be 1.84); δ, the difference between the two sets of numerical variables (estimated to be 1); Zα, the standard normal value corresponding to the inspection level α; and Zβ, the standard normal value corresponding to β. If *σ* = 1.8 months, *δ* = 1 month, *α* = 0.05, *β* = 0.20, Zα/2 = Z0.05/2 = 1.96, and Zβ =Z0.20 = 0.842; then, by substituting the above formula, we obtain$${n}_1={n}_2=2{\left[\frac{\left(1.96+0.842\right)\times 1.8}{1}\right]}^2=50.9\approx 51$$

Hence, 51 cases will be included in the control group and 51 cases in the experimental group, with the total sample size being 102 cases.

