### Data analysis

After the last patient completes the follow-up study, the committee will assess the occurrence of the primary and secondary endpoints. Treatments in participant timeline are all routine medical orders, and patients will follow the medical advice. If there is any failure to review on time, a phone call will be reminded. If the patient fails to complete the relevant examination, evaluation or follow-up within the agreed time, or cannot suspend the study, part of the clinical trial of the patient will be suspended. The data of these patients will be marked on the record and not entered in the final curative effect analysis system. The fixed staff is responsible for the input of data, coded into groups 1 and 2 according to their treatment plans, and set a password for the database to protect the privacy of patients’ data. Data quality is controlled by the Data Quality Supervision Committee.

Data will be organized and analyzed using the SPSS 25.0 software, and *P* < 0.05 will be considered significant in all statistical tests. iPFS and OS will be calculated using the Kaplan-Meier method. Assessment of neurological function will be scored using the EDSS assessment scale, and QoL will be scored using the FACT-G. The chi-squared test will be used in combination with propensity matching analysis to minimize differences due to smoking, sex, weight loss, geographic factors, economic status, and education level and to avoid baseline effects to the greatest extent possible. Definition of analysis population relating to protocol non-adherence is that the patients who do not follow. In addition, we use the multiple imputation method to handle missing data.

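### Scan gaps of 2 and 6 months, timed differently on the iPFS clock in each arm, do not fit a Kaplan-Meier analysis of a 1-month difference

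*Protocol article*

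**What the plan says.** Five statements in the protocol article bear on this point.

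- **Scan schedule** (Post TOMO follow-up): "After radiotherapy, patients will be reviewed every 2 months for a total of 6 months to evaluate whether they have recurrence". Then "During 6 months to 2 years after treatment, a re-check will be performed every 6 months". On content: "The examination will include a brain MRI test, routine blood tests, and liver and kidney function tests". On length: "The follow-up period for iPFS and OS is 2 years". Imaging is therefore due at 2, 4, 6, 12, 18 and 24 months after radiotherapy.
- **Follow-up frequency in the abstract** (Methods): "Follow-up consultations will be conducted every 2 months", with no later change of interval.
- **Effect scale** (Sample size): the design effect is "the difference between the two sets of numerical variables (estimated to be 1", in months, and the SD entered in the formula is 1.8 months.
- **Clock** (Primary study outcome): iPFS is counted in months from the start of radiotherapy to the first evidence of progression. The Treatment plan section gives the experimental arm 20 fractions in 4 weeks. The control arm has 20 whole-brain fractions followed by a 9-fraction sequential boost.
- **Analysis** (Data analysis): "iPFS and OS will be calculated using the Kaplan-Meier method". Interval censoring and unscheduled imaging are not mentioned anywhere in the article.

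**The concern.** Progression seen on MRI is known only to have happened between the last clear scan and the first positive one. Here that window is 2 months wide early on and 6 months wide later, which is 2 to 6 times the difference the trial is designed to find. Kaplan-Meier on detection dates treats the end of the window as the event time.

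Two things are at stake. The first is the estimate: a difference in median months read from such curves mostly reflects where the scans fall. The second is more serious and concerns the comparison itself. The clock starts when radiotherapy starts, but the scan calendar starts when it ends, and the control course has more fractions. The same biological progression time is then recorded later in control patients than in experimental patients. This is a systematic difference between arms, not noise.

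**Working it through.** **The plan's own figure.** n per arm = 2 × [(1.96 + 0.842) × 1.8 / 1]² = 50.9, so 51. This reproduces.

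**Assumptions.** No control median iPFS is stated, so a range of 2 to 12 months was used. Times are either normal with SD 1.8 (the sample-size model) or exponential, with a true median 1 month longer in the experimental arm and 51 patients per arm. Each progression is dated at the next scheduled scan. The Data analysis section names no test for comparing the curves, so the log-rank test, two-sided at 0.05, is assumed.

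**Step 1: medians, scans aligned in both arms.** Take control 8 and experimental 9 months, SD 1.8.
- Progressed by month 6: Φ((6 − 8)/1.8) = Φ(−1.11) = 13% control; Φ((6 − 9)/1.8) = Φ(−1.67) = 5% experimental.
- Progressed by month 12: Φ(2.22) = 99% and Φ(1.67) = 95%.

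Both scan-dated medians are 12 months, so the difference is 0. In simulation:
- SD 1.8: 3 against 4 months gave a difference of 0 (49%) or 2 (51%); 5 against 6 gave 0 (50%) or 6 (50%); 8 against 9 gave 0 (100%).
- Over all control medians, the difference was 0, 2 or 6 months in 99.9–100% of trials under SD 1.8 and in 79–96% under exponential times.
- It fell between 0.5 and 1.5 months in 0% of trials under either model. With exact dates, about 73% of trials fall in that range under SD 1.8.

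**Step 2: log-rank power, scans aligned.** Under SD 1.8, exact dates give about 0.70–0.75. Scan dates give about 0.72 at a control median of 4 months, 0.67 at 6 and 0.43 at 8. Under exponential times there is almost no loss.

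**Step 3: the offset.** At an assumed 5 fractions per week:
- Experimental: 20/5 = 4.0 weeks = 4.0 × 7/30.4 = 0.92 month.
- Control: 29/5 = 5.8 weeks = 5.8 × 7/30.4 = 1.33 months.
- Difference: 0.41 month.

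On the iPFS clock the scans around the first long gap fall at 6.92 and 12.92 months (experimental) and at 7.33 and 13.33 months (control). The possible median differences become about −0.4, 1.6 and 5.6 months.

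For 8 against 9 months, SD 1.8:
- Experimental in the gap: Φ(2.18) − Φ(−1.16) = 0.985 − 0.124 = 86%, all dated 12.92.
- Control in the gap: Φ(2.96) − Φ(−0.37) = 0.998 − 0.355 = 64%, all dated 13.33.

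At 12.92 months almost every remaining experimental patient has an event while every remaining control patient is counted as progression-free.

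Share of simulated trials with a significant log-rank result, true benefit in the experimental arm:

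| Model, control median | Aligned: for experimental | Offset: for experimental | Offset: for control |
|---|---|---|---|
| SD 1.8, 4 months | 0.72 | 0.18 | 0.002 |
| SD 1.8, 6 months | 0.67 | 0.03 | 0.04 |
| SD 1.8, 8 months | 0.43 | 0.00 | 0.95 |
| SD 1.8, 10 months | 0.52 | 0.00 | 0.99 |
| SD 1.8, 12 months | 0.62 | 0.002 | 0.53 |
| Exponential, 4 months | 0.20 | 0.02 | 0.06 |
| Exponential, 8 months | 0.09 | 0.02 | 0.03 |

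An interval-censored model given the same offset intervals was never significant for control under SD 1.8.

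**Step 4: which gap matters.** The Background section hypothesises a 5–8% gain in iPFS time. That equals 1 month only if baseline iPFS is 1/0.08 = 12.5 to 1/0.05 = 20 months, where scans are 6 months apart.

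**The case against.** **Analysis detail belongs in a statistical analysis plan.** Dating rules and the choice of model are often left there, and none is shown. The protocol does not say that a difference in medians is the primary estimate, and its definition of progression does not confine detection to scheduled scans. This is fair, and it makes dating at the scan an assumption. But the protocol itself fixes the clock, the scan calendar, the effect in months and the Kaplan-Meier method, and these do not fit together as written.

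**Much of the instability is sampling error.** Under exponential times, even exact dates put the median difference within 0.5–1.5 months in only 31%, 21% and 17% of trials at control medians of 4, 6 and 8 months. This stands for that model. Under the plan's SD of 1.8 the scan grid is the main cause.

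**A reader might infer a general loss of power**, or add a rounding variance to the 1.8 months and put the result back into the sample-size formula. The documents do not support either. With 6-month gaps and SD 1.8, most of an arm can fall in one interval, so the rounding error is neither independent nor uniform, and the formula compares means while the analysis is Kaplan-Meier. With aligned scans the simulated loss is small up to control medians of about 6 months.

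**The remedy cannot find what was not observed.** With aligned scans and no dropout, a nonparametric interval-censored curve equals Kaplan-Meier at the scan dates and says nothing between them. This stands: there is no power gain in that case. The benefit comes from the offset. It is also why the 6-month rate should come from the model, since on the iPFS clock neither arm has a scan at exactly 6 months.

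**The abstract's schedule may be shorthand.** Possibly, but it still differs from the detailed text, and a 2-month grid is also coarser than 1 month.

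**Conclusion.** The concern holds in this form. A scan-dated difference in medians moves in steps of about 0, 2 or 6 months, or about −0.4, 1.6 and 5.6 with the offset, and does not estimate a 1-month gain. The medians themselves sit on scan dates; 0, 2 and 6 describe the difference between them.

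The effect on the test depends on conditions. With aligned scans it is small, except when both medians lie well inside a 6-month gap and times are as tightly spread as the plan's SD of 1.8 implies: power then falls from about 0.70 to about 0.43 at a control median of 8 months.

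The offset between arms is the stronger reason to act. Under SD 1.8 and control medians of 8–10 months it turned a true experimental benefit into a significant result for control in at least 95% of simulated trials.

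A reader might conclude that the trial will reverse its result. The documents do not support that. Reversal depends on dating at the scan, an assumed 5 fractions per week for the boost, assumed control medians and the narrow SD. Under exponential times the offset removes most of the already low power but does not produce reversal.

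**What to change.** In Data analysis, make the main iPFS analysis interval-censored. Each progression should lie between the last scan without it and the first scan with it, both measured from the start of radiotherapy. Report a hazard ratio and a 6-month iPFS rate from that model, in place of a difference in scan-dated medians. Keep Kaplan-Meier with a log-rank test as supportive.

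Reconcile the abstract's 2-monthly follow-up with the schedule under Post TOMO follow-up.

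The cost is analysis wording, a less familiar method and possibly software other than SPSS. No extra scans are needed. The change brings no power gain if the arms' scans turn out to be aligned.

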**Fig. 2 Fig2:**
[figure not shown]
Flow chart representing the study procedures

**Table 2 Tab2:** Summary of the research outline

	Study period						
	Run-in		Treatment				Follow-up
Time point	***-2W***	0W	***1W***	***2W***	***3W***	***4W***	***104W***
Visit	Visit1	Visit2	Visit3	Visit4	Visit5	Visit6	Visit7
**Enrollment**							
Eligibility screen	√	√					
Informed consent	√						
Demographics	√						
Randomization		√					
**Intervention**							
Experimental group							
Control group							
**Assessments**							
iPFS						**√**	**√**
Neurological function		√	√	√	√	√	√
QoL		√	√	√	√	√	√
OS						**√**	**√**

*W* week or weeks, *iPFS* intracranial progression-free survival, *QoL* quality of life, *OS* overall survival

### Data analysis

After the last patient completes the follow-up study, the committee will assess the occurrence of the primary and secondary endpoints. Treatments in participant timeline are all routine medical orders, and patients will follow the medical advice. If there is any failure to review on time, a phone call will be reminded. If the patient fails to complete the relevant examination, evaluation or follow-up within the agreed time, or cannot suspend the study, part of the clinical trial of the patient will be suspended. The data of these patients will be marked on the record and not entered in the final curative effect analysis system. The fixed staff is responsible for the input of data, coded into groups 1 and 2 according to their treatment plans, and set a password for the database to protect the privacy of patients’ data. Data quality is controlled by the Data Quality Supervision Committee.

Data will be organized and analyzed using the SPSS 25.0 software, and *P* < 0.05 will be considered significant in all statistical tests. iPFS and OS will be calculated using the Kaplan-Meier method. Assessment of neurological function will be scored using the EDSS assessment scale, and QoL will be scored using the FACT-G. The chi-squared test will be used in combination with propensity matching analysis to minimize differences due to smoking, sex, weight loss, geographic factors, economic status, and education level and to avoid baseline effects to the greatest extent possible. Definition of analysis population relating to protocol non-adherence is that the patients who do not follow. In addition, we use the multiple imputation method to handle missing data.

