### Primary study outcome

#### Intracranial progression-free survival

The primary study outcome is iPFS, defined as the number of months from the start of TOMO or conventional 3D-CRT/IMRT to the occurrence of the first evidence of disease progression, which will be evaluated according to the Response Evaluation Criteria in Solid Tumors.

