#### Overall survival

Overall survival (OS) refers to the number of months between the radiotherapy procedure and the time of death or last follow-up. For patients who are lost to follow-up prior to death, the time of the last follow-up visit is usually calculated as the time of death.

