## Dissemination

### Data monitoring

The Data Monitoring Committee (DMC) is composed of all the authors, with [name] as the team leader, responsible for testing the accuracy and authenticity of data and reviewing whether the operation of obtaining data is standardized. If the patient fails to complete the relevant examination, evaluation, or follow-up within the agreed time or cannot suspend the study, part of the clinical trial of the patient will be suspended.

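### Removing patients with missed assessments from the efficacy analysis selects the compared groups after randomisation and conflicts with the overall survival rule

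*Protocol article*

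**What the plan says.** The trigger is in the Data analysis section: "If the patient fails to complete the relevant examination, evaluation or follow-up within the agreed time, or cannot suspend the study". Part of that patient's trial participation is then suspended, and the consequence for the analysis follows: "The data of these patients will be marked on the record and not entered in the final curative effect analysis system". The same section adds, without naming variables: "In addition, we use the multiple imputation method to handle missing data". Its sentence on the analysis population breaks off: "Definition of analysis population relating to protocol non-adherence is that the patients who do not follow". No set of all randomised patients is named anywhere in the article.

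The Overall survival section treats loss to follow-up differently: "For patients who are lost to follow-up prior to death, the time of the last follow-up visit is usually calculated as the time of death".

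The primary endpoint is a time: "The primary study outcome is iPFS, defined as the number of months from the start of TOMO or conventional 3D-CRT/IMRT" to first evidence of progression. The stated method is "iPFS and OS will be calculated using the Kaplan-Meier method", with 2 years of follow-up.

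The Data monitoring section repeats the trigger ("If the patient fails to complete the relevant examination, evaluation, or follow-up within the agreed time") and the suspension, but not the removal from the analysis.

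**The concern.** Allocation is 1:1 at random, so the arms are comparable at the start. A rule that keeps or drops a patient according to later attendance can undo this. Participants are not blinded, and progression, side effects or the treatment itself may affect who attends over 2 years. If missed visits are related to outcome and are more frequent in one arm, the retained groups differ for reasons other than the effect of treatment. The primary endpoint is exposed to this as well as OS.

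The exclusion is also unnecessary for the method chosen. Kaplan-Meier can use a patient's event-free time up to the last assessment.

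Three instructions can apply to the same patient: removal, imputation and, for OS, a death dated at the last visit. Unless the plan says which one governs, the choice could be made after the data are seen. Finally, the sample size equals the calculated number exactly, so any exclusion comes out of the planned power.

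**Working it through.** **1. The plan's own figure.** Inputs from the Sample size section: SD 1.8 months, difference 1 month, 1.96 and 0.842.

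n per arm = 2 × [(1.96 + 0.842) × 1.8 / 1]² = 50.88, rounded up to 51.

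This reproduces the plan. The one-sided test named in the text (0.05, SD 1.8) would give 41 per arm, so 51 rests on the two-sided value.

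**2. Power after exclusions.** Power = Φ(1 / (1.8 × √(2/n)) − z), with n = 51 × (1 − d). The article gives no exclusion share d, so the values of d are assumptions.

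| Share excluded (assumed) | n per arm | 1/(1.8√(2/n)) | Power, z = 1.96 (as calculated) | Power, z = 1.645 (one-sided, as worded) |
|---|---|---|---|---|
| 0% | 51 | 2.805 | 80.1% | 87.7% |
| 10% | 45.9 | 2.661 | 75.9% | 84.5% |
| 20% | 40.8 | 2.509 | 70.9% | 80.6% |
| 30% | 35.7 | 2.347 | 65.1% | 75.9% |

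As calculated, losing one patient per arm (n = 50) already gives 79.3%.

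To keep 51 analysable per arm, 51/(1 − d) must be randomised: 57 at 10%, 64 at 20% and 73 at 30%. That restores power but leaves the bias.

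**3. Illustration of bias.** All inputs are assumed: exponential iPFS with median 5 months in both arms (no true effect), and patients progressing before month 6 excluded with probability p.

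- Rate λ = ln 2 / 5 = 0.1386; mean 1/λ = 7.213 months.
- P(T < 6) = 1 − e^(−6λ) = 0.5647.
- Contribution to the mean from T < 6: 7.213 × [1 − e^(−6λ)(1 + 6λ)] = 1.462.
- Retained mean = (7.213 − 1.462p) / (1 − 0.5647p).
- Retained median: the time at which half of the retained fraction (1 − 0.5647p) has progressed.

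| p | Share of arm removed | Retained mean | Retained median |
|---|---|---|---|
| 10% | 5.6% | 7.49 | 5.36 |
| 20% | 11.3% | 7.80 | 5.83 |
| 30% | 16.9% | 8.16 | 6.34 |

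At 20% v 10% the means differ by 0.31 month. At 30% v 10% the means differ by 0.67 month and the medians by 0.98 month.

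**4. The statements side by side.** A patient lost to follow-up before death meets the Data analysis trigger and is removed, yet the Overall survival section keeps that patient with a death at the last visit. Both cannot hold for OS. Imputation and removal can coexist only if imputation is confined to gaps in retained patients, which the text does not say.

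**The case against.** Several stronger readings are tempting, and the article does not support them.

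- **That every late visit means removal.** The section first provides a telephone reminder, and only part of the patient's participation is suspended. The unfinished population sentence leaves the scope unclear. A patient who progressed or died before the missed visit already has an event, and the text does not clearly say that such a patient is dropped. The Data monitoring section supports the suspension only. What stands is that removal from the efficacy analysis is stated outright.
- **That multiple imputation is flatly contradicted.** Missing baseline covariates or questionnaire items in retained patients could still be imputed. The two statements are unreconciled rather than strictly contradictory.
- **That the planned power is lost.** Under the one-sided test named in the text, power stays above 80% at 20% exclusion. No exclusion rate is given, and the formula compares means although iPFS is a time to event. The percentages therefore describe the plan's own calculation and not the Kaplan-Meier comparison.
- **That missed visits track deterioration, so both arms look too good and any imbalance becomes a false effect.** A link with deterioration is plausible, but the article gives no data on it or on a difference between arms.
- **That the illustrative bias is a given fraction of the planned 1-month difference.** The assumed exponential has an SD of about 7 months, while the 1 month was planned with SD 1.8. In SD units, 0.67/7.2 is about 0.09, against 1/1.8 = 0.56 planned. Simulating a two-sided log-rank test under the same assumptions (51 per arm, 24 months) puts the false-positive rate at about 5.5% with no exclusion and about 7% at 30% v 10%. Equal exclusion of 10% in both arms gave no material inflation.

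An article may leave detail to a fuller plan. That does not answer this point, because the exclusion rule is stated and not omitted.

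**Conclusion.** The rule is wrong as written and must be changed before the final analysis. It chooses the analysed groups on an event after randomisation, for the primary endpoint as well as OS, and nothing else in the article restores an all-randomised analysis. The conflict with the Overall survival section is direct, whereas the multiple imputation statement needs reconciling.

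The size of the bias cannot be fixed from the article. It depends on whether missed visits are related to outcome and differ between arms, and the month figures are illustrations only. The power loss is secondary: about 4, 9 and 15 percentage points at assumed exclusions of 10%, 20% and 30% under the calculation as made. Under the one-sided wording, power falls below 80% only beyond about 20% exclusion.

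**What to change.** - Delete the sentence that keeps these patients out of the efficacy analysis.
- Complete the population definition: the primary analysis includes all randomised patients in the arm assigned.
- For iPFS, censor event-free patients at the last evaluable brain MRI. For OS, censor patients not known to have died at the date last known alive, replacing the rule that counts the last visit as death.
- State that multiple imputation applies to the quality-of-life and neurological scores and to missing covariates, not to iPFS or OS.
- Keep the completers-only set as a sensitivity analysis. Censoring at the last assessment also assumes that loss is unrelated to outcome, so report missed assessments by arm.

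The cost is a wording change in the protocol or analysis plan, made before outcomes are compared by arm. The affected patients are already to be marked on the record, so no new patients or visits are needed.
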